#### Blinding

Participants and their caregivers will be informed about the study aims and procedures, but they will be blinded to group allocation. In the case the patient asks for the presence of the caregiver, she/he will be seated near the participant but out of her/his view, without interfering during the treatment session. The OT/PT performing the intervention will not be blinded to the group allocation. Outcome assessments will be administered and scored by a member of the staff blinded to group allocation.

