Several studies support the application of VR methods in the rehabilitation of the hemiplegic upper limb in stroke patients [26]. The largest study conducted to date involved 376 patients and demonstrated a positive effect of VR-based rehabilitation [27]. Moreover, recent literature reviews [28] have provided evidence for improvement in upper limb motor function and daily life activity after VR-based training compared with standard interventions. However, clinical evidence based on rigorous RCTs on the effect of the combined use of observation of actions followed by their immediate imitation in a VR environment (AO + VR therapy) is lacking, especially in the case of rehabilitation applied during the chronic phase after a stroke.

The main hypothesis of the study is that, for the recovery of motor function of hemiplegic stroke patients in the chronic phase, a combined rehabilitation treatment (AO + VR therapy) is more effective than a control treatment (control observation – CO) based on the observation of videos without motor content (e.g., environmental natural scenes), followed by the execution of actions in VR (CO + VR control therapy).

In sum, the planned trial will examine the following hypotheses:

AO + VR is an effective tool for promoting upper limb control in paretic stroke patients, and its effects are greater than CO + VR control treatment.Motor performance, cognitive level, and structural brain damage assessed before treatment are correlated to the degree of improvement resulting from the AO + VR intervention.The AO + VR intervention results in greater plastic functional changes of the MNS activity compared with the effects of the CO + VR control treatment.

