## Methods/Design

### Study design

This study will consist in a multicentric randomized allocation concealed (waitlist-controlled) and evaluator-blinded clinical trial (RCT) with two investigative arms, using an intensive rehabilitation program based on AO followed by imitation in VR (AO + VR) (experimental intervention) compared with a control treatment based on observation of control videos (CO) followed by action execution in VR (CO + VR) (control intervention) (see Fig. 1 for a visualization of the flow diagram of the RCT in accord with CONSORT guidelines). This study protocol is in line with the recommendations for clinical trials (SPIRIT) guidelines (Additional file 1).

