#### *Experimental treatment (AO* + *VR)*

Participants of the experimental group will undergo a treatment based on observation of actions followed by their immediate reproduction in VR (AO + VR treatment). The experimental treatment will consist in 18 sessions lasting about 1 h each, with a tolerance of ± 2 sessions, thus resulting in a minimum of 16 and a maximum of 20 sessions. Treatment sessions will be carried out with a frequency of about four days per week, within a period of five weeks. During the rehabilitation sessions, the patient will be instructed to carefully watch videos lasting about 1.5 min, presented on the monitor, consisting in unimanual or bimanual actions performed by an actor, from a lateral perspective (see Fig. 2-B1). Subsequently, the patient will be asked to imitate the actions presented for at least three consecutive times, within a time window of 3 min., using the same objects observed in the video, in a virtual scenario (VR), through the Khymeia VRRS system. During the execution of all exercises, the patient will wear also kinematic sensors for three-dimensional tracking of the performed movement, aimed to control objects in the virtual scenario. The treatment will include a total of 52 exercises, arranged as simple movements and complex sequences, either unimanual or bimanual, of increasing complexity. Examples of the proposed exercises are reported in Additional file 2. The protocol will include, for each week of training, a set of exercises subdivided in two parts, the first to be performed for two days, and the remaining to be performed in the remaining two days. For each exercise, the therapist will set the facilitation level, adjusting the sensitivity of kinematic sensors (levels range from 1 to 10) according to the patient's manual impairment. Facilitation level will be used particularly for those patients showing minimal residual hand ability, allowing them to perform the VR exercises. In more details, the exercises during the first week will include “no-gravity” movements (with no hand lifting) such as sliding to reach for a target located in different positions. The second and the third weeks will consists of “simple” and “complex” anti-gravity actions (requiring arm/hand lifting) respectively, either unimanual or bimanual. Furthermore, some bimanual functional exercises will be introduced, such as to put the toothbrushes in a glass, or to use knife and fork. The fourth week will consist of complex bimanual daily life actions, such as, for example, to wear sunglasses, or to draw a line with the ruler. Finally, during the fifth week, a set of more complex anti-gravity exercises will be proposed, including tasks of obstacles avoiding or following a path using a graspable floating pad device. Each session of AO + VR rehabilitation will take 30–45 min. to complete, including changing the setting between different exercises. The administration of personalized set of exercises will be adapted based on the patient hand motor performance at baseline, thus patients with minimal hand and arm ability will perform only no-gravity movements and simple anti-gravity actions, while patients with discrete hand ability will also perform the advanced exercises. Despite this type of adjustment of the treatment all the recruited patients will receive an equal number of treatment sessions, thus the final dose of the treatment will be balanced between the experimental and the control group.

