
#### *Control treatment (CO* + *VR)*

Participants randomly assigned to the control group will receive an equal number of rehabilitation sessions, as the experimental group. Differently from the latter, patients of the control group will be required to observe videos depicting naturalistic scenes (Fig. 2-B2), without motor contents, for 1.5 min. Then, they will receive a motor training in the VR environment, performing the same type of exercises included in the above-described experimental treatment, prompted by the verbal instructions of an expert therapist. Thus, the general setting for carrying out the rehabilitation sessions will be identical to that of the experimental group, except for the fact that the control group will not be involved in action observation before preforming the exercises. Thus, the control treatment is not based on action imitation, but on purely motor execution.

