#### Recruitment

Patients considered eligible (see Methods section “Inclusion and Exclusion criteria”) will be invited from the “Cardinal Ferrari Center” and the “Clinical Institute Quarenghi” to participate in the trial, explaining them in detail the purposes and methods of the study. Before enrollment, the informed consent (see Additional file 3) will be obtained from patients, or from the caregivers.

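### The Blinding section says participants are blinded to allocation, but as described they are not: they are told the aims and procedures, and the two arms are openly different

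*Protocol article*

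**What the plan says.** All places are in the protocol article.

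- **Blinding:** "Participants and their caregivers will be informed about the study aims and procedures, but they will be blinded to group allocation". The same section says "The OT/PT performing the intervention will not be blinded to the group allocation" and that a blinded staff member administers and scores the outcome assessments. A caregiver attends a session only if the patient asks, sits outside the patient's view and does not interfere.
- **Recruitment:** eligible patients are invited by "explaining them in detail the purposes and methods of the study". The consent form is Additional file 3, which is not shown.
- **Background, first hypothesis:** "AO + VR is an effective tool for promoting upper limb control in paretic stroke patients, and its effects are greater than CO + VR control treatment".
- **Experimental treatment:** videos of about 1.5 minutes, "consisting in unimanual or bimanual actions performed by an actor, from a lateral perspective", followed by imitation in virtual reality (VR).
- **Control treatment:** "patients of the control group will be required to observe videos depicting naturalistic scenes", also for 1.5 minutes, followed by the same type of VR exercises on the therapist's verbal instruction. The section adds that "the control treatment is not based on action imitation, but on purely motor execution".
- **Study design:** the trial is labelled an "evaluator-blinded clinical trial (RCT"; the label does not mention participants.
- **Primary outcome:** the BBT, a timed dexterity test, at baseline, after treatment (T1) and at six months (T2).

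**The concern.** Blinding to allocation needs one of two things. Either the arms look alike to the participant, or the participant lacks the information to tell which arm is which. The article describes neither. The video content and the way the exercise is prompted differ visibly at every session, over 16 to 20 sessions, and the participant has been told what the study is for and how it works. No withheld hypothesis, partial disclosure or masking of the videos is described.

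The BBT score depends on how hard the patient tries within a fixed time. Hope in the action-observation arm, or disappointment in the control arm, would both act in the direction of the hypothesis, and an unblinded therapist delivers the sessions. A final report that repeats the participant-blinding claim would overstate what a positive result shows. Patients who know their arm can also reveal it to the assessor, whose blinding is the one well-founded safeguard.

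**Working it through.** **1. The passages side by side**

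| What blinding of participants needs | What the article describes |
|---|---|
| Arms that look alike | Different videos (actor's actions or natural scenes) and different prompting (imitation or verbal instruction) |
| Or no knowledge of what each arm is | Aims and procedures disclosed (Blinding); purposes and methods explained in detail (Recruitment) |
| Or a stated device, such as a withheld hypothesis | None described |

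None of the three is met by the text. The claim is also wider than the Study design label, which covers the evaluator only.

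**2. The plan's own figure**

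The inputs come from Sample size (difference 7 points at T1, SD 11.3, power 80%, dropout 10%) and Statistical analyses (two-sided 5%).

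- Normal approximation: n = 2 × (1.960 + 0.842)² × (11.3/7)² = 40.9, so 41 per group; 41/0.9 = 45.6, so 46.
- Exact two-sample t-test: 41.9 per group; 41.9/0.9 = 46.5, so 47.

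The stated 47 per group reproduces. There is no numerical error, and the blinding point does not depend on this figure.

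**3. Illustration of size**

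The documents give no expectation effect. The shifts below are assumptions: 1 and 2 blocks, which are 1/7 = 14% and 2/7 = 29% of the target difference. Evaluable patients are 47 × 0.9 = 42.3, taken as 42 per group. The test is the independent-samples t-test that the plan names for the primary endpoint, applied to BBT at T1 with SD 11.3.

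- SE = 11.3 × √(2/42) = 2.47.
- Rejection probability with no true effect and shift b = P(Z > 1.96 − b/SE) + P(Z < −1.96 − b/SE).
- b = 1: b/SE = 0.41, giving 6.9%.
- b = 2: b/SE = 0.81, giving 12.8%.
- The noncentral t with 82 df gives 6.9% and 12.6%.

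So the nominal 5% becomes about 7 to 13% under these assumed shifts.

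**The case against.** The strongest reply is that the consent form is not shown. A patient will see which kind of video is played. Whether the patient knows that it is the favoured or the comparison condition depends on how the aims are worded. Being informed of aims and procedures need not mean being told which arm is expected to win. This stands as a limit: the article does not prove that every patient will know. But the detailed explanation described under Recruitment points the other way. If the consent form does restrict disclosure, the Blinding section fails to say so and still needs correcting.

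The control is also a good one: equal sessions, the same type of exercises, videos of equal length and an otherwise identical setting. With a blinded assessor, this limits attention and detection bias, and it deserves credit. It does not reach the patient's own expectation.

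Caregivers attend only on request and out of the patient's view. That protects the patient from their influence; the article does not say that the screen or the instructions are hidden from the caregiver.

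Two stronger readings are tempting and are not supported:

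- A reader might infer that the protocol claims protection from expectation effects. It never mentions them. The design label is confined to the evaluator, and the therapist is openly unblinded.
- A reader might infer that assessor blinding is already compromised. Nothing in the text suggests this. The risk is only that informed patients could disclose their arm, and the detailed instructions against it may sit in the full protocol.

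**Conclusion.** The point holds as a mismatch within the document: the Blinding section states a property that the described design does not deliver and that the Study design label does not claim. It rests on the text as written under Blinding, Recruitment and the two treatment sections; the unseen consent form could soften it but not make the wording accurate.

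No sample size or analysis changes. The possible bias on the BBT is real in direction but unknown in size. The 7 to 13% error rate is an illustration that rests on an assumed shift of 1 to 2 blocks, 42 evaluable patients per group and the planned t-test. A reader might quote larger figures from a more precise, baseline-adjusted analysis. Those would need a correlation that the documents do not give, and a test other than the one named for the primary endpoint.

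This should be corrected, because blinding is a core item in judging risk of bias and the correction costs little. It does not invalidate the trial.

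**What to change.** 1. In the Blinding section, state that outcome assessors are blinded, that therapists are not, and that participants cannot be blinded to the type of video they receive.
2. In the patient information, describe the comparison neutrally: two kinds of video before VR training are compared, without saying which is expected to do better. If this is done, claim at most that participants are unaware of the study hypothesis. If it is not done, make no claim of participant blinding.
3. Instruct participants and caregivers not to mention the videos to the assessor at any BBT assessment after treatment has begun (T1 and T2).
4. Optional: have the assessor record a guess of the arm after the T1 and T2 BBT.

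The cost is wording in the protocol and patient information, an ethics notification for the revised information and, if item 4 is adopted, one line on the case report form. The downside is that the trial is described as less blinded. Study Status says that recruitment had not started at submission, so the patient information could be revised before the first patient. If recruitment has since begun, items 1 and 3 can still be adopted, and the final report should not repeat the participant-blinding claim.

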#### Data management

Each participating center will send the case report form (CRF) to the data manager and the principal investigator of the study (AE). The file will be encrypted, and password protected. All requests for database changes will be tracked and stored. Neuroimaging data acquired at Parma University Hospital will be transferred via Digital Imaging and Communications in Medicine (DICOM) protocol to the Picture Archive Computed System (PACS) for the management of diagnostic images in digital format and will be available for performing the statistical analysis.

At the beginning of the study, to each patient will be assigned an alphanumeric identification code, which does not allow to directly identify the patient’s name. All data collected during the study, except for demographical ones, will be recorded, processed, and stored together with this code. Only the data manager and authorized staff members will be able to associate this code with the patient’s name.

### Statistical analyses

#### Analysis of primary and secondary outcomes measures

Clinical data will be managed and analyzed using the Statistical Package for Social Sciences (SPSS version 21.0). Descriptive statistics will include standard median, deviation, and interquartile distance calculated for both experimental and control groups. For the evaluation of the primary endpoint, the t-Student test for independent samples will be used. In case of excessive deviation from normality, similar non-parametric test (Mann Whitney) will be used.

The primary analysis will be carried out on all participants enrolled in the study, according to the *intention-to-treat* principle. Changes in motor performance between T0 and the subsequent longitudinal evaluations (T1, T2) will be assessed using the repeated measures Analysis of Variance (rmANOVA) with a mixed design 2 × 3, considering the group as “between subjects” factor and the time point measure (T0, T1, T2) as “within subjects” factor.

Missing data will be treated implementing a linear mixed model (LMM) on a “long” database, avoiding “listwise deletion” (elimination of all information related to the subject with missing data). The estimation of parameters deriving from the mixed model will be compared with that related to the rmANOVA analysis, also to assess the impact of missing data. The analyses related to the secondary endpoints will be carried out by applying the same LMM model. Statistical significance will be set at two-tailed alpha error values of *P* < 0.05.

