### Participants

In general, eligible patients will be adults with a clinical diagnosis of stroke (from 3 to 18 months after the acute event, controlled via medical history and patient’s data in the respective rehabilitation center), resulting in primarily motor symptoms with unilateral upper limb paresis and residual movement ability. Only patients with severe motor symptoms or further severe neuropsychological deficits will not be eligible to participate. The multicentric study will take place in two clinical centers representing the main Italian venues for stroke rehabilitation based on VR, i.e., the “Cardinal Ferrari Center” (S. Stefano Riabilitazione) (Parma, IT) and the “Clinical Institute Quarenghi” (Bergamo, IT).

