### Outcomes

#### Primary outcome

The primary outcome measure will be the Box and Block Test (BBT) [31, 32], a timed test for assessing upper limb dexterity and motor coordination. The test consists of 150 small wooden cubes (25 mm side) contained in a wooden box. The assessment will be performed by an investigator blinded to the assignment of the patient to the experimental or control group, before treatment (T0), after the conclusion of the treatment (T1, within 72 h of conclusion) and after 6 months, as a follow-up (T2).

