#### Sample size

According to CONSORT guidelines [38, 39], the estimated sample size is based on projected treatment effects on the primary outcome measure, the BBT. Based on the available literature [32], we consider a 7-point change in BBT scores at post-test (T1) as a clinically significant effect. Based on a common standard deviation at post-test equal at 11.3 and a drop-out rate of 10%, we estimate that a sample of 47 subjects for each group (*N* = 94) will have a statistical power of 80% to detect a significant difference between the two measurements.

Concerning the fMRI study, the sample size estimate is based on the calculation of the level of change in the Blood Oxygenation Level Dependent (BOLD) signal detected in a previous fMRI study with an action observation paradigm (number of subjects per group = 10). Significant activation clusters within the MNS, including the PMv and the IPL, were considered for the analysis, using a statistical threshold of *p* < 0.001 with Family Wise Error (FWE) correction for multiple comparisons at the cluster level. The Power Analysis (software: NeuroPower-tool) conducted on this study showed that to obtain a change in the BOLD signal with a significance threshold of *p* < 0.05 and a minimum statistical power of 80% with Bonferroni correction, it is necessary to recruit at least 9 participants per group. However, regardless of the presence or absence of effects at the group level, patients will also be treated as a case-series, so that assessment of BOLD change following treatment will also be performed at the single case level.

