### Assignment of intervention

#### Randomization

Participants will be randomly assigned to either control or experimental group with a 1:1 allocation using a computer-generated randomization schedule, stratified by clinical level of the hand use (minimal vs. discrete). In particular, permuted blocks of random sizes will be used. The block sizes will not be disclosed, to ensure concealment. All randomization, sequence generation, and preparation of group allocation materials will be performed by an independent researcher, who has no direct contact with the clinical aspects of the trial.

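### The primary Box and Block Test comparison is a valid, correctly sized t-test, but it has no term for baseline score or the hand-use stratum and so leaves precision unused

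*Protocol article*

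**What the plan says.** All references are to the protocol article.

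- **Primary test** (Analysis of primary and secondary outcomes measures): "For the evaluation of the primary endpoint, the t-Student test for independent samples will be used". The fallback is also unadjusted: "In case of excessive deviation from normality, similar non-parametric test (Mann Whitney) will be used". No covariate is named, and the section does not say whether the variable is the T1 score or the change from T0.
- **Measurement times** (Primary outcome): BBT is assessed "before treatment (T0), after the conclusion of the treatment (T1, within 72 h of conclusion) and after 6 months, as a follow-up (T2"), so a baseline value is planned for every patient.
- **Allocation** (Randomization): 1:1 and "stratified by clinical level of the hand use (minimal vs. discrete"). Centre is not a stratification factor.
- **Sizing** (Sample size): "we consider a 7-point change in BBT scores at post-test (T1) as a clinically significant effect". The calculation is "Based on a common standard deviation at post-test equal at 11.3 and a drop-out rate of 10" per cent, and gives 47 per group for 80% power.
- **Other models** (same analysis section): a 2 × 3 repeated-measures ANOVA with group and time, and a linear mixed model to handle missing data. Both take T0 as one level of the outcome. Neither names the hand-use stratum.

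**The concern.** Two pieces of information that bear on a patient's T1 score are known before treatment: the T0 score on the same test, and the hand-use class used to stratify allocation. The named primary test uses neither, unless it is run on change scores.

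The two omissions have different consequences.

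- **Baseline.** Differences between patients that were already present at T0 stay in the error term. The interval has correct coverage but is wider than it needs to be.
- **Stratum.** Stratified allocation removes hand-use imbalance from the treatment difference. A plain t-test still estimates its standard error as if that imbalance could occur, so the standard error is too large for the design actually used. The test then rejects less often than 5% under the null hypothesis, and its interval over-covers.

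At stake is how precisely the trial can report its main result from 94 patients.

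**Working it through.** **1. Reproduce the stated sample size.** Inputs from Sample size: difference 7, SD 11.3, 80% power, dropout 10%. From the analysis section: two-sided alpha 0.05.

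- Standardised difference: 7 / 11.3 = 0.619.
- The noncentral-t solution for two independent means is 41.9, so 42 per arm.
- Dropout: 42 / 0.90 = 46.7, so 47 per arm and N = 94. This matches exactly.
- Power with 42 analysed per arm: 80.1%.

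The sample size is therefore that of an unadjusted comparison of T1 scores, with no credit taken for baseline.

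**2. Adjust for baseline.** The documents give no T0–T1 correlation ρ, so a range is assumed. The residual SD is 11.3 × √(1 − ρ²). The 95% CI half-width is t × SD × √(2/42), with t ≈ 1.99. Unadjusted: 1.989 × 11.3 × 0.2182 = 4.9 blocks.

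| Assumed ρ | Residual SD | Power for 7 blocks | CI half-width (blocks) |
|---|---|---|---|
| no adjustment | 11.30 | 80.1% | 4.9 |
| 0.3 | 10.78 | 83.7% | 4.7 |
| 0.5 | 9.79 | 90.0% | 4.2 |
| 0.7 | 8.07 | 97.5% | 3.5 |
| 0.8 | 6.78 | 99.7% | 2.9 |

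**3. If the t-test is meant for change scores.** Assuming SD 11.3 at both visits, the change-score variance is 2(1 − ρ) × 11.3². Divided by the ANCOVA variance (1 − ρ²) × 11.3², this gives 2/(1 + ρ): 1.54 at ρ = 0.3, 1.33 at 0.5, 1.18 at 0.7 and 1.11 at 0.8. Power of the change-score test with 42 per arm is 65.9%, 80.1%, 95.2% and 99.3% respectively. It equals the raw T1 comparison at ρ = 0.5, is worse below that, and is below ANCOVA throughout.

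**4. Omit the stratum.** Let R² be the share of BBT variance explained by hand use (not documented; assumed 10%, 25% and 40%). With strata balanced between arms, the true variance of the treatment difference is (1 − R²) times what the t-test estimates. The true type I error is then approximately 2 × [1 − Φ(1.96 / √(1 − R²))].

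| Assumed R² | 1.96 / √(1 − R²) | True type I error | Power, unadjusted → stratum-adjusted (simulated) |
|---|---|---|---|
| 10% | 2.07 | 3.9% | 81% → 84% |
| 25% | 2.26 | 2.4% | 83% → 90% |
| 40% | 2.53 | 1.1% | 86% → 95% |

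Simulation with 42 per arm and two equal strata gives the powers shown. Its type I errors agree with the formula to within about 0.2 percentage points, and adjusting for the stratum brings the error back to about 5%.

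Steps 2 and 4 are separate calculations. Hand use and baseline BBT probably carry much of the same information, so the gains must not be summed.

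**The case against.** The strongest reply is that nothing here is an error. The t-test is a valid comparison of randomised groups, the trial is sized for exactly that test, and the type I error is not inflated. All of this stands. A reader might infer that the trial is underpowered or its intervals invalid, and the documents support neither. Too wide in the literal sense applies only to the omitted stratum. For baseline, the interval is merely wider than necessary.

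A second reply is that the plan does use T0, through the repeated-measures ANOVA and the mixed model. That is true, so it would be wrong to say the plan throws the baseline away. But neither model is the one named for the primary endpoint, and neither names the stratum. With T0 as an outcome level, the group-by-time contrast from T0 to T1 is, with complete data, a change-score comparison, which step 3 shows to be less efficient than ANCOVA.

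A third reply is that the gains rest on undocumented inputs. This also stands. At a correlation of 0.3 the gain in power is under four percentage points, and at R² = 10% the test is only mildly conservative.

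A reader might also add centre to the charge, since "The multicentric study will take place in two clinical centers". Centre is not a randomisation factor, so omitting it does not distort the standard error as omitting the stratum does, and nothing documents that the centres differ in BBT.

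**Conclusion.** The point holds as a matter of efficiency and of matching the analysis to the randomisation. The stated N and 80% power are correct for the stated test.

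Its size depends on two quantities the documents do not give. Over assumed T0–T1 correlations of 0.3 to 0.8, baseline adjustment narrows the 95% CI half-width from 4.9 to between 4.7 and 2.9 blocks and raises power from 80% to between 84% and 99.7%. Over assumed stratum shares of 10% to 40%, the unadjusted test runs at 3.9% down to 1.1% instead of 5%. The direction is the same across both ranges; only the amount is uncertain.

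The unstated choice between T1 score and change score needs settling in any case. If change scores were intended and the correlation were below 0.5, the planned N would give less than 80% power (with equal SDs at T0 and T1, as in step 3).

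**What to change.** - Make the primary analysis an ANCOVA of T1 BBT with arm, baseline BBT and hand-use stratum as terms. Report the adjusted difference with its 95% CI.
- Alternatively, use the T1 contrast of the mixed model already planned, with baseline BBT and stratum as covariates and T1 and T2 as the outcome levels.
- State that the outcome is the T1 score. Keep the unadjusted t-test or Mann-Whitney as a sensitivity analysis, so that a normality check cannot drop the adjustment from the primary result.
- Keep N = 94 and describe the 80% power as conservative.
- A centre term is optional. Adding centre as a randomisation stratum is a separate design preference and not part of this point.

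The cost is a change of wording: no new data, no more patients, and one or two residual degrees of freedom. Study Status says recruitment has not started at submission, so the change can be made before any outcome data exist.

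### The primary analysis of the Box and Block Test is not uniquely fixed, and the test named for it cannot deliver the stated intention-to-treat analysis

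*Protocol article*

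**What the plan says.** All analysis statements are in the protocol article, section 'Analysis of primary and secondary outcomes measures'. They come in this order:

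- An independent-samples t-test is assigned to the primary endpoint. No time point is given, nor whether the score or the change from T0 is compared. A fallback follows: "In case of excessive deviation from normality, similar non-parametric test (Mann Whitney) will be used".
- The next paragraph sets the population: "The primary analysis will be carried out on all participants enrolled in the study", by intention to treat. Its next sentence reads "Changes in motor performance between T0 and the subsequent longitudinal evaluations (T1, T2) will be assessed using the repeated measures Analysis of Variance (rmANOVA" and specifies group by three time points (T0, T1, T2).
- Missing data are handled by an LMM on long-format data, chosen to avoid listwise deletion. "The estimation of parameters deriving from the mixed model will be compared with that related to the rmANOVA analysis". The same LMM is used for the secondary endpoints.
- One threshold covers everything: "Statistical significance will be set at two-tailed alpha error values of *P* < 0.05".

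The section 'Primary outcome' lists BBT at T0, T1 and T2 without marking one as primary. T1 is singled out only under 'Sample size': "we consider a 7-point change in BBT scores at post-test (T1) as a clinically significant effect".

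**The concern.** Two analyses have a claim to be primary: the t-test, through the phrase about the primary endpoint, and the rmANOVA, through the intention-to-treat sentence that leads into it. The LMM stands beside them as a comparison. If they disagree, nothing in the article settles the result.

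The population statement also does not match the named test. Without imputation, a t-test or Mann-Whitney uses only patients who have the analysed value. A classical rmANOVA uses only patients with all three visits, so someone with valid T0 and T1 values but no six-month visit is lost. The plan recognises listwise deletion as a problem and already has the remedy, but it does not give that remedy the primary role.

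At stake are a clear reading of the trial's result and, if the choice of deciding test stays open until the data are seen, the 5% error rate.

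**Working it through.** **1. Reproduce the sample size.** Inputs from 'Sample size': difference 7, SD 11.3, dropout 10% ("Based on a common standard deviation at post-test equal at 11.3 and a drop-out rate of 10" per cent), power 80%. The two-sided 0.05 comes from the statistical section.

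- Normal approximation: n = 2(1.96 + 0.8416)² × (11.3/7)² = 2 × 7.849 × 2.606 = 40.9, so 41 per arm; 41/0.9 = 45.6, so 46.
- Exact t-test: 41.9, so 42 per arm; 42/0.9 = 46.7, so 47.

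This matches the plan: "a sample of 47 subjects for each group (*N* = 94) will have a statistical power of 80" per cent. The trial was therefore sized on a two-group comparison at T1 by t-test, using the SD of the post-test score, not on the rmANOVA or the LMM. This is the basis for reading the t-test as a T1 test.

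**2. Who is analysed.** At the plan's own 10% loss, 94 × 0.9 = 84.6, so about 9 to 10 of the 94 would be absent from an analysis that needs complete data. The 10% is tied to the T1 calculation; the article gives no separate figure for loss by six months.

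| Method | Patients used without imputation |
|---|---|
| t-test or Mann-Whitney | those with the analysed value |
| 2 × 3 rmANOVA | those with T0, T1 and T2 |
| LMM | those with at least one BBT value |

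**3. Error rate, conditional on the reading.**

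- If one test decides, the error rate is 5%. In null simulation each test alone rejected in about 5% of runs.
- If either of two tests could be claimed as success, the figure under independence is 1 − 0.95² = 9.75%.
- Simulation with 47 per arm, normal data, equal correlation between visits, and random dropout of 5% by T1 and 10% by T2 (8,000 runs per scenario, Monte Carlo error about 0.35 points) gave, for the T1 t-test or the rmANOVA group-by-time interaction, 9.5%, 9.6% and 9.9% at correlations 0.5, 0.7 and 0.85. With no missing data at 0.7 it gave 8.8%.
- A separate simulation with 42 per arm and three other correlation patterns gave 9–10%.
- If the t-test were on change from T0, counting that test, the interaction and the LMM as three routes gave about 8–9%.

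The correlations and the dropout pattern are assumptions; the article gives neither.

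**4. What a baseline-adjusted T1 contrast gives at the same N.** With T0–T1 correlation r, the SD becomes 11.3 × √(1 − r²) (ANCOVA approximation). With 42 per arm evaluable, power ≈ Φ(7/SD × √(42/2) − 1.96), where √21 = 4.583.

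| r (assumed) | SD | 7/SD × 4.583 | Power |
|---|---|---|---|
| unadjusted | 11.30 | 2.84 | 81% (80% by exact t) |
| 0.5 | 9.79 | 3.28 | about 90% |
| 0.7 | 8.07 | 3.97 | about 98% |

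**The case against.** The best defence is that a primary test is named. The t-test is tied to the primary endpoint, the sample size places it at T1, and 47 per arm reproduces on that basis. The rmANOVA has its own stated purpose (change over time), and so does the LMM (missing data and secondary endpoints). Read this way, one test decides and the error rate is 5%. Mann-Whitney replaces the t-test and is not an additional test. Missing data are also not ignored, since the plan adopts the LMM to keep partial records.

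Most of this stands, and it rules out several stronger readings that a reader might infer:

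- *That the 5% error rate fails.* The article never allows success on any test. The 9–10% applies only if it did. The 5% is not guaranteed by the text, but it is not shown to be broken.
- *That the rmANOVA would be underpowered.* This could be said only of the group main effect, which averages in T0. The group-by-time interaction is the natural treatment test in this design. For a sustained 7-block benefit at 42 per arm it had about 80%, 94% and 99% power under the three correlation patterns simulated.
- *That six-month attrition weakens the T1 t-test.* It does not; that test loses only patients without a T1 value.
- *That a tipping-point analysis or centre adjustment is missing.* Such detail can be left to the analysis plan.

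The defence leaves some gaps. T1 has to be inferred from another section, and score or change is not stated. The trigger for Mann-Whitney has no criterion, and that test does not address the 7-block mean difference used for sizing. The primary-analysis sentence still runs into the rmANOVA. The named t-test still cannot include everyone enrolled, and there is no order of precedence. These problems lie in what the article states, not in detail it left out.

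**Conclusion.** The concern holds as an ambiguity with an internal conflict, and it should be fixed. The primary analysis is not uniquely fixed. The test tied to the primary endpoint does not fit the stated population, and the one planned method that keeps patients with missing visits has only a supporting role for BBT.

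The error rate is 5% if the T1 t-test alone decides. It is about 9–10% if either that test or the rmANOVA interaction could be claimed, under the assumed correlations and random dropout. The sample size is sound for a T1 comparison and is not in question.

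**What to change.** State one confirmatory test: the arm difference in BBT at T1 from the LMM, adjusted for baseline BBT and the hand-use randomisation stratum, in all randomised patients with BBT data, two-sided 0.05. State how baseline enters the model. If T0 is a response with the arms held equal at baseline, patients with only a T0 value also stay in. Say that T2 from the same model is secondary. Label the t-test, Mann-Whitney and rmANOVA as supportive, so that none of them can decide the trial.

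The cost is a few sentences and slightly more modelling. The LMM is already planned, no new data are needed, and N = 94 is unchanged. Power at T1 rises above 80% to the extent that T0 and T1 correlate: about 90% at 0.5 and about 98% at 0.7, both assumed. The article reports that recruitment had not begun at submission; the choice should in any case be fixed before unblinded data are seen.
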